**Other secondary endpoints**

The analysis of the other secondary endpoints will be provided in the SAP.

**11.5.2 Safety Analyses**

Usual descriptive statistics will be used and detailed in the SAP to analyze the safety parameters as follows:

- Deaths, SAEs, TEAEs and bleeding events, and of patients withdrawn because of safety concerns.
- Type, time of occurrence post dosing, frequency, seriousness, severity and relatedness of IMP emergent adverse events (TEAEs) will be analyzed. TEAEs will be analyzed according to current version of the MedDRA (Medical Dictionary for Regulatory Affairs) dictionary.
- Vital signs will be described and analyzed as needed at the various time-points across the whole study period.
- Laboratory abnormalities will be described and listed by dose level and for the placebo. Reference will be made to multiples of the upper normal limit (UNL) as defined by the laboratory’s specifications. Shift tables will be issued.
- Immunogenicity will be analyzed both in frequency (including the presence of non-clinically relevant ADA) and severity if clinically expressed, and per dose-group level.

### **11.5.3 Pharmacokinetic Endpoints Analysis**

Pharmacokinetics will be described using all time-points and will be represented graphically.

## 12. QUALITY CONTROL/ MONITORING

Monitoring is the act of overseeing the progress of a clinical trial, and of ensuring that it is conducted, recorded, and reported in accordance with the protocol, Standard Operating Procedures (SOPs), Good Clinical Practice (GCP), and the applicable regulatory requirement(s).

The main responsibilities of the CRA are to verify investigators' adherence to the protocol and that informed consent is obtained and recorded for all patients prior to implementation of any study procedure.

The CRA will contact and visit the investigator at regular intervals during the study. He will compare the CRFs with medical records and other relevant documentation through direct access, during the on-site monitoring visits. He ensures the completeness, consistency and accuracy of the data being recorded in the CRF by the investigator. Monitoring activities will be adapted according to local guidelines provided by competent authorities during the COVID-19 pandemic period.

The CRA will explain the protocol and study related procedures to all study staff, including the investigator. If new collaborators are included during the course of the study, additional training sessions will be organised by the investigator and/or the CRA.

As part of the supervision of the study progress other sponsor personnel or the CRO may, on request, accompany the CRA on visits to the study site. The investigator and his collaborators commit to cooperate with the CRA to resolve any problems, corrections, or possible misunderstandings concerning the findings detected in the course of these monitoring visits.

## 13. RESPONSIBILITIES

### 13.1 SPONSOR'S RESPONSIBILITIES

The sponsor or its representative will submit an application to Ethics Committees//Institutional Review Boards (whether central or local) and Competent Authorities for approval of the clinical study. A copy of the Ethics Committee's/IRB's and Competent Authorities' approvals must be received by the sponsor before the study starts.

In accordance with the provisions of the law and the GCP, the sponsor will have an insurance policy intended to guarantee against possible damage resulting from the research.

The studies and/or experiments performed on behalf of the sponsor will be specifically and expressly guaranteed. It is advisable to underline that noncompliance with the Research Legal Conditions is a cause for guarantee exclusion.

### 13.2 INVESTIGATOR'S RESPONSIBILITIES

The investigator is responsible for ensuring the accuracy, completeness, legibility, and timeliness of the data reported. All source documents should be completed in a neat, legible manner and kept up-to-date to ensure accurate interpretation of data.

The investigator will maintain adequate and accurate records in accordance with ICH Good Clinical Practice to enable the conduct of the study to be fully documented and the study data to be subsequently verified for trial-related monitoring, audits, IRB/IEC review, and regulatory inspection.

Agreement of the investigator to conduct and administer this study in accordance with the protocol will be documented in separate study agreements.

The investigator will be responsible for giving information and training about the study to all staff members involved in the study or in any element of subject management, both before

starting the practical performance of the study and during the course of the study (e.g., when new staff become involved).

The investigator will maintain a record of all individuals involved in the study (medical, nursing and other staff) and will specify, for each person, the tasks delegated for the study. The investigator is responsible for ensuring the privacy, health, and welfare of the patients during and after the study.

The investigator must be familiar with the background and requirements of the study and with the properties of the investigational product as described in the SmPC/USPI/IB/Product Labeling Information as well as the synthetic data for the use of IMP.

## **14. CONFIDENTIALITY AND ARCHIVING**

### **14.1 PERSONAL DATA PROTECTION AND CONFIDENTIALITY**

The Sponsor (or the delegated representative) is the data controller of the study and the protocol will be conducted in accordance with the European Regulation No. 2016/679 of 27 April 2016 (General Data Protection Regulation) and national law.

The patients will be informed by the information and consent form that their personal data collected for the purpose of the study will be kept confidential and will be processed by the Sponsor and its representatives. The patients will also be informed of their rights according to General Data Protection Regulation.

The investigator must assure that the personal data of patients, including their identity and all other personal medical information, will be kept confidential at any time.

Patient number and initials will identify the patients in the CRF. On other documents or photographic materials (including the results of imaging) submitted to the sponsor, patients will not be identified by their names but by an identification code (e.g. patient number).

By signing this protocol, the investigator undertakes that the protocol and all attached information are and will remain confidential. The investigator agrees that after providing the protocol and all information necessary for the personnel involved, he remains responsible for their total confidentiality. Such obligation is detailed in the confidentiality agreement signed by the investigator before the initiation of the study.

The investigator agrees that, subject to local regulations and ethical considerations, a sponsor representative or any regulatory agency may consult directly and/or copy study documents in order to verify a case report, provided that the subject's identity remains anonymous.

The investigator undertakes to treat all subjects data used or disclosed in connection with the conduct of study in compliance with European and local applicable laws relating to data protection.

The investigator will be responsible for keeping a list of all enrolled patients including patient numbers, full names and date of birth.

### **14.2 STUDY DOCUMENTATION & ARCHIVING**

The investigator must maintain adequate and accurate records to enable the conduct of the study to be fully documented and the study data to be subsequently verified. The study documents, including patient CRFs, should be classified in the investigator's file.

The investigator's file will contain the protocol/amendments, independent ethics committee and health authorities with correspondence, sample informed consent, IMP records, staff curriculum vitae and authorization forms, correspondence, etc.

The investigator must keep the Study File until the Sponsor authorization of destruction and by default during at least 15 years after completion or discontinuation of the study.

Should the investigator wish to assign the study records to another party or move them to another location, the sponsor must be notified in advance.

## **15. ETHICAL AND REGULATORY ASPECTS**

### **15.1 PATIENT'S INFORMATION NOTE AND WRITTEN CONSENT FORM**

The information note must be given to the patients before their decision to participate or abstain from participation, according to local requirements and Good Clinical Practice. This information is based on the elements set out in the Declaration of Helsinki and the ICH-GCP Guidelines. It must also describe the measures taken to safeguard patient's privacy and protection of personal data, according to European RGPD. Restraints and risks must be explained, as well as the right to discontinue participation in the study at any stage, without affecting their further relationship with the investigator and/or their future care.

The information note and written consent form must be submitted by the investigator to the patient with an oral explanation. The consent must be agreed and signed by the patient or legal representant according to local regulations before any study-related procedure starts.

Moreover, regarding the population to be included emergency consent procedure will be implemented in the study. The procedure will be adapted in each country according to local regulation on emergency consent and inclusion procedures. Consent confirmation will be systematically done when patient become able of consent by themselves in accordance to local regulation requirement.

The consent form is made in duplicate: the original copy is kept by the Investigator and one copy is given to the patient.

If any information becomes available during the trial that may be relevant to the patient's willingness to keep on participating in the trial, an updated written informed consent must be submitted to the patient to confirm his agreement to continue participating.

### **15.2 ACCESS TO SOURCE DATA**

The investigator must authorize the Clinical Research Associate (CRA) to have direct access to all source documents concerning the patient necessary for the verification of data listed in the CRF.

At the time of the visit of the CRA, the investigator must provide the CRA with printouts of electronic medical files, signed by the investigator. The CRA must date and sign all pages of each printout after comparing them to the CRF.

In case of requests from the Health Authorities, The Investigator will permit direct access to all study documents, IP accountability records, medical records and source data.

According to ICH-GCP requirements, the patient will be informed in writing about the need for Source Data Verification (SDV) for quality control, and audits/inspections.

### **15.3 STUDY CONDUCT**

The study will be conducted according to the ICH Good Clinical Practices standards, Declaration of Helsinki, as well as any European and/or local applicable laws and regulations relating to the conduct of the study.

### **15.4 ETHICS COMMITTEES AND COMPETENT AUTHORITIES**

This protocol and other documents (e.g. Investigator's Brochure, Patient Information, etc.) will be submitted by the sponsor/CRO to an IEC/IRB. Before starting the study, the investigator

must have received written approval of the Study Protocol and the Patient Information Consent Form from the IEC/IRB. The IEC/IRB approval must reveal the Study Protocol version as well as the documents reviewed.

During the study, the sponsor must inform the IEC of any changes to the protocol, all SUSARs and any new information that may affect the safety of the patients or the conduct of the study. As required by local regulations, the sponsor and the investigators, are required to verify that all legal aspects are respected and that the approval of the relevant regulatory authorities where appropriate has been obtained, prior to study initiation.

The Summary of Product Characteristics and/or the Investigator's Brochure/The operating instructions, the Study Protocol, the name and site of the investigators, the opinion of the IEC(s)/IRBs will be submitted to the National Authorities before the beginning of the study. The relevant local authorities have to be informed by the sponsor about the clinical study implementation and its status.

## **15.5 AMENDMENTS**

Neither the investigator nor the sponsor may alter the protocol without the authorization of the other party. Any amendment that may be issued, must be dated and signed by both parties and must appear as an amendment to the protocol before implementation.

Substantial amendments are submitted for opinion/approval/authorization to IEC/IRB and CA before implementation.

Substantial amendments on safety measures are submitted for approval/authorization to EC and CA but could be implemented immediately under specific conditions defined with the sponsor.

## **15.6 AUDIT AND INSPECTION**

The investigator must accept that the source documents for this trial should be made available to auditors (qualified personnel from the sponsor or its designees) or to Health Authority inspectors after appropriate notification. The CRF data verification must be carried out by direct control of source documents. The investigator will be available to answer any question asked by the auditors/inspectors and will make every effort to facilitate the proper conduct of the audit/inspection.

In case of inspection, the investigator will inform the sponsor who should participate to the inspection.

## **16. PUBLICATION OF DATA**

The data and research results are the exclusive property of the sponsor. No information or publication may be made without prior authorization of the sponsor.

The sponsor reserves the right to publish or use them in any form whatsoever, to submit them to Health Authorities of any country, on behalf or on behalf of its subsidiaries.

Should the study generate results likely to be patented, then only the sponsor will be authorized to file such a patent, in his name and at his expenses.

The final clinical study report will be written according to the ICH E3 Guideline (Structure and Content of Clinical Study Reports) and according to all applicable regulations.

## 18. APPENDICES

### Appendix 1: NEWS-2 Scale

| National Early Warning Score (NEWS)* |       |          |             |             |             |           |            |
|--------------------------------------|-------|----------|-------------|-------------|-------------|-----------|------------|
| PHYSIOLOGICAL PARAMETERS             | 3     | 2        | 1           | 0           | 1           | 2         | 3          |
| Respiration Rate                     | ≤8    |          | 9 - 11      | 12 - 20     |             | 21 - 24   | ≥25        |
| Oxygen Saturations                   | ≤91   | 92 - 93  | 94 - 95     | ≥96         |             |           |            |
| Any Supplemental Oxygen              |       | Yes      |             | No          |             |           |            |
| Temperature                          | ≤35.0 |          | 35.1 - 36.0 | 36.1 - 38.0 | 38.1 - 39.0 | ≥39.1     |            |
| Systolic BP                          | ≤90   | 91 - 100 | 101 - 110   | 111 - 219   |             |           | ≥220       |
| Heart Rate                           | ≤40   |          | 41 - 50     | 51 - 90     | 91 - 110    | 111 - 130 | ≥131       |
| Level of Consciousness               |       |          |             | A           |             |           | V, P, or U |

*Appendix 2: WHO COVID-19 Ordinal Scoring Scale*

| Patient State                          | Descriptor                                            | Score |
|-----------------------------------------------|--------------------------------------------------------------|--------------|
| Uninfected                      | No clinical or virological evidence of infection             | 0            |
| Ambulatory                      | No limitation of activities                                  | 1            |
|                                               | Limitation of activities                                     | 2            |
| Hospitalized
Mild disease   | Hospitalized, no oxygen therapy                              | 3            |
|                                               | Oxygen by mask or nasal prongs                               | 4            |
| Hospitalized
Severe Disease | Non-invasive ventilation or high-flow oxygen                 | 5            |
|                                               | Intubation and mechanical ventilation                        | 6            |
|                                               | Ventilation + additional organ support – pressors, RRT, ECMO | 7            |
| Dead                            | Death                                                        | 8            |

*Appendix 3 : Conversion tables for estimation of PaO2 and FiO2*[figure not shown]**Instructions to complete the CRFs****Conversion tables****1 Estimating PaO2 from a given SO2**

| SO 2 (%) | PaO 2 (mmHg) |
|---------------------|-------------------------|
| 80                  | 44                      |
| 81                  | 45                      |
| 82                  | 46                      |
| 83                  | 47                      |
| 84                  | 49                      |
| 85                  | 50                      |
| 86                  | 52                      |
| 87                  | 53                      |
| 88                  | 55                      |
| 89                  | 57                      |
| 90                  | 60                      |
| 91                  | 62                      |
| 92                  | 65                      |
| 93                  | 69                      |
| 94                  | 73                      |
| 95                  | 79                      |
| 96                  | 86                      |
| 97                  | 96                      |
| 98                  | 112                     |
| 99                  | 145                     |

**2 Estimating FiO2**

| Method                   | O 2 flow (l/min) | Estimated FiO 2 (%) |
|--------------------------|-----------------------------|--------------------------------|
| Nasal cannula            | 1                           | 24                             |
|                          | 2                           | 28                             |
|                          | 3                           | 32                             |
|                          | 4                           | 36                             |
|                          | 5                           | 40                             |
|                          | 6                           | 44                             |
| Nasopharyngeal catheter  | 4                           | 40                             |
|                          | 5                           | 50                             |
|                          | 6                           | 60                             |
| Face mask                | 5                           | 40                             |
|                          | 6-7                         | 50                             |
|                          | 7-8                         | 60                             |
| Face mask with reservoir | 6                           | 60                             |
|                          | 7                           | 70                             |
|                          | 8                           | 80                             |
|                          | 9                           | 90                             |
|                          | 10                          | 95                             |

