#### 5.1.1 Inclusion Criteria

1. Male or female hospitalized patients  $\geq 18$  years (i.e., at least 18 years old at the time of randomization) and  $< 80$  years, having given their written consent.
2. Having a positive RT-PCR or antigenic test for COVID-19, or with a highly positive serology AND clear symptoms of COVID-19,
3. Presenting with symptoms of COVID-19, including:
  - Cough
  - OR

- Shortness of breath or difficulty breathing  
OR at least 2 of the following
  - Fever, defined as any body temperature  $38^{\circ}\text{C}$
  - Chills
  - Repeated shaking with chills
  - Muscle pain
  - Headache
  - Sore throat
  - New loss of taste or smell
4. Presenting with signs of moderate but progressive pulmonary disease in the last 48 hours with:
- Respiratory symptoms (cough, dyspnea, etc.),
  - Uni- or bilateral ground-glass opacities, or pulmonary infiltrates on chest radiograph and/or CT scan performed within the past 96hrs,
  - Clinical and/or biological evidence of progression over the past 48hrs.
  - Progression will be assessed as follows:
    - symptom worsening: increase in the number of symptoms, and/or in the intensity of some of them  
And/or
    - worsening of respiratory condition: increase in respiratory rate and/or decrease of  $\text{PaO}_2/\text{FiO}_2$  in ambient air  
And/or
    - worsening of biological markers: CRP increase or increase of other severity/prognostic markers, and/or increase of D-Dimers
5. Presenting with a **moderate** respiratory distress defined as:
- a) At least one of the following signs associated with the onset of ARDS:
- Respiratory rate (RR)  $\geq 24/\text{min}$ ,  
OR
  - $\text{SpO}_2 \leq 93\%$  in ambient air. In case where oxygenotherapy cannot be discontinued, please refer to NEWS 2 Scale (item  $\text{SpO}_2$ , scale 2) for adequate conversion (e.g. 93-94 on  $\text{O}_2$  corresponding to 86-87 in ambient air),  
OR
  - $\text{PaO}_2/\text{FiO}_2 \leq 200\text{mmHg}$  (please refer to Appendix 3 for conversion).
- AND**
- b) NOT in a **severe** respiratory distress defined as:
- Respiratory rate (RR)  $< 30/\text{min}$ ,  
And
  - $\text{PaO}_2/\text{FiO}_2 > 100\text{mmHg}$ .

6. Presenting with signs of a pro-thrombotic status characterized by:

- a. D-Dimers  $\geq 0.5 \mu\text{g/mL}$ ,
  - b. and/or Troponin T  $> 2.5 \mu\text{g/L}$  (or by default Troponin I greater than local laboratory reference),

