## 7.3 BASELINE / RANDOMIZATION

Randomization will be performed automatically via the IxRS by the site. Detailed procedure will be described in the dedicated instruction manual. The following examination will be performed before randomization. General and specific examinations and tests that are part of the standard-of-care for Covid-19 management are not study specific and results can be used for the screening/eligibility assessment of the patients before the signature of the informed consent.

- Validation of eligibility criteria assessed during screening visit
- Vital signs (BP, Pulse); 1-time-point pharmacokinetics (baseline);
- Blood sample for Anti-glenzocimab antibodies (ADA) assessments will be collected and sent to the central laboratory;

- Soluble GPVI will be collected and sent to the central laboratory;
- Local blood sample test;
- Respiratory distress parameters:
  - Respiratory Rate (RR),
  - Oxygen saturation (SpO2),
  - PaO2/FiO2 (please refer to Appendix 3 for conversion);
- Chest CT-scan (to be repeated only if the previous one done more than 48 hrs prior to randomization);
- NEWS-2 and/or WHO scales;
- Concomitant medication;
- Recording of adverse events according to NCI-CTCAE;
- IxRS (Randomisation and Day 1 kit allocation).

The randomization visit should be performed within 24 hrs after the screening visit, once all eligibility criteria have been collected and checked.

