#### **Primary efficacy endpoint: Progression from moderate to severe respiratory distress assessed at Day 4**

Progression from moderate to severe respiratory distress assessed at Day 4 is a composite failure endpoint defined as the occurrence of at least one of the following failure events at Day 4 :

- $RR \geq 30/\text{min}$ , or
- $SpO_2$  decrease  $> 5\%$  in ambient air. In case where oxygenotherapy cannot be discontinued, please refer to NEWS 2 Scale (item  $SpO_2$ , scale 2) for adequate conversion (e.g. 93-94 on  $O_2$  corresponding to 86-87 in ambient air),
- $PaO_2/FiO_2 \leq 100\text{mmHg}$
- Death occurring prior to or on Day 4

The composite event rate will be estimated within each group. The difference in composite event rates and the odds ratio will be estimated along with their asymptotic and exact 95% confidence intervals. p-values from the chi-square and exact Fisher test will also be provided.

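### Appendix 3 gives a plain face mask at 7 L/min two FiO2 values, so the PaO2/FiO2 limit of 100 mmHg can be passed or missed by the same patient at SpO2 86 to 90%

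*Protocol*

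**What the plan says.** Protocol Appendix 3 contains two look-up tables under the heading "Instructions to complete the CRFs".

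- Table 1 is for "Estimating PaO 2 from a given SO 2" and has one PaO2 for each whole percentage of saturation from 80 to 99.
- Table 2 turns device and oxygen flow into an "Estimated FiO 2". For a plain face mask it has three rows: 5 L/min is 40%, 6-7 L/min is 50% and 7-8 L/min is 60%. The nasal cannula, nasopharyngeal catheter and reservoir mask each have one value per flow.

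The appendix is cited in two settings:

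- **Eligibility.** Section 5.1.1, item 5a, accepts PaO2/FiO2 at or below 200 mmHg as one of three alternative signs and adds "please refer to Appendix 3 for conversion". Item 5b of the same criterion then requires both a respiratory rate below 30/min and PaO2/FiO2 above 100 mmHg. The synopsis version puts both limits, 100 and 200, on the line that cites the appendix, though there as one of several possible signs.
- **Baseline.** Section 7.3 lists "PaO 2 /FiO 2 (please refer to Appendix 3 for conversion" among the respiratory parameters.

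PaO2/FiO2 at or below 100 mmHg is also a component of the primary endpoint in Section 11.5.1, which is "defined as the occurrence of at least one of the following failure events at Day 4". The hypoxemia status in Section 9.1 uses cut-points of 100, 200 and 300 mmHg. Neither of these sections, nor the Day 4 visit in Section 7.7, cites Appendix 3.

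**The concern.** A flow of 7 L/min by plain face mask belongs to both the 50% row and the 60% row. The protocol gives no tie-break, and it contains no other conversion for PaO2/FiO2. Up to 11 sites (7 in France and 4 in Brazil, per the synopsis) would each choose a row.

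The choice matters if it moves the ratio across a limit that decides something. The limit of 100 mmHg separates moderate from severe: above it a patient can enter, and at or below it a patient meets a failure component. Two sites with identical readings could then disagree on whether a patient may enter and, if they use the table at Day 4, on whether that component has failed. The trial's stated aim is to estimate a treatment difference from about 30 evaluable patients per arm, so each reclassified patient moves an arm's observed event rate by 1/30, or 3.3 percentage points.

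**Working it through.** **Inputs.** PaO2 for each SpO2 from Appendix 3, table 1. FiO2 of 0.50 (row 6-7 L/min) and 0.60 (row 7-8 L/min) from table 2. Limits of 100 and 200 mmHg from Sections 5.1.1, 9.1 and 11.5.1. The overlap concerns look-up values, so there is no derived figure in the plan to reproduce first.

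**Formula.** PaO2/FiO2 = table 1 PaO2 divided by table 2 FiO2 as a fraction.

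| SpO2 (%) | PaO2 (mmHg) | Ratio at 0.50 | Ratio at 0.60 | At or below 100? |
|---|---|---|---|---|
| 85 | 50 | 100.0 | 83.3 | yes / yes |
| 86 | 52 | 104.0 | 86.7 | no / yes |
| 87 | 53 | 106.0 | 88.3 | no / yes |
| 88 | 55 | 110.0 | 91.7 | no / yes |
| 89 | 57 | 114.0 | 95.0 | no / yes |
| 90 | 60 | 120.0 | 100.0 | no / yes |
| 91 | 62 | 124.0 | 103.3 | no / no |

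Over the whole of table 1 (80 to 99%), the two rows disagree on the 100 mmHg limit at exactly 86, 87, 88, 89 and 90%. The upper end is exact: 60/0.60 = 100, which counts as at or below the limit. On the 200 mmHg limit they disagree only at 98% (112/0.50 = 224; 112/0.60 = 186.7).

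If PaO2 is measured and only FiO2 is taken from the table, the disagreement covers PaO2 above 50 mmHg (0.50 × 100) and up to 60 mmHg (0.60 × 100).

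**Entry.** At SpO2 86 to 90% both rows give a ratio below 200, so item 5a is met either way. Item 5b is met on the 50% row and not on the 60% row. With a respiratory rate below 30/min and all other criteria met, the row alone decides entry.

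**Hypoxemia status, if derived from the table.** SpO2 86 to 90% is moderate on one row and severe on the other. SpO2 98% is mild (224) on one and moderate (186.7) on the other.

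**Day 4 composite, if derived from the table.** The row changes the composite only when respiratory rate is below 30/min, the patient is alive and the SpO2 component has not failed. That last component uses the same saturation reading. Taking its decrease of more than 5% as an unconverted absolute fall from baseline, which is an assumption, the Day 4 values at which the row still decides are:

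| Baseline SpO2 (%) | Day 4 SpO2 at which the row decides (%) |
|---|---|
| 91 or less | 86-90 |
| 92 | 87-90 |
| 93 | 88-90 |
| 94 | 89-90 |
| 95 | 90 |
| 96 or more | none |

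The protocol asks for a conversion when oxygen cannot be stopped and gives one example, 93-94 on oxygen as 86-87 in ambient air. If that 7-point gap is assumed constant, all of 86-90% flips only with a baseline ambient-equivalent SpO2 of 84% or less, 90% alone flips at 88%, and nothing flips at 89% or more.

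**The case against.** A reader might infer that any patient at SpO2 86 to 90% on a 7 L/min mask is a primary-endpoint failure or not according to the row. The documents do not support this, for two reasons. The endpoint is a composite in which one failed component suffices, and the SpO2 component will often have failed already at these saturations. Also, neither the endpoint definitions nor the Day 4 visit cites Appendix 3. The CRF-instructions heading, and the absence of any other conversion, make its use at Day 4 a reasonable inference and no more.

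A reader might also take the 98% crossing of 200 mmHg as a second eligibility error. That limit is one of three alternatives in item 5a, so it matters only when the respiratory rate is below 24/min and the converted SpO2 is above 93%. With the assumed 7-point gap, 98% would convert to 91% and qualify anyway. A changed entry decision is not shown there.

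Finally, the problem touches one device at one flow with estimated FiO2, in an exploratory trial. The study is double-blind (Section 6.3.2), so the choice of row should not follow treatment: this is misclassification noise, and a bias towards either arm should not be inferred.

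All of this stands and limits the size of the point. It does not remove the overlap or its effect on item 5b, where the criterion itself sends sites to the appendix.

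**Conclusion.** The point holds as a minor defect. Appendix 3 contradicts itself at 7 L/min for a plain face mask. At SpO2 86 to 90% the two rows give opposite answers on the mandatory entry limit of more than 100 mmHg. This follows exactly from the protocol's own tables, provided that both PaO2 and FiO2 are estimated from them.

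The effect on the Day 4 PaO2/FiO2 component and on hypoxemia status depends on the further inference that the same table is used at those assessments. The effect on the composite depends in addition on no other component having failed. The protocol does not say how many patients would be on this device and flow with an estimated FiO2. The number is probably small.

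**What to change.** Reconcile the two face-mask rows of Appendix 3, table 2, so that 7 L/min maps to a single FiO2. The documents do not show which value is intended, so the sponsor has to settle it. Apply that one mapping to the recorded device and flow for all sites, at entry and at Day 4, so that the ratio does not depend on which row a site reads.

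The cost is one table correction and one programmed derivation. Sample size, visits and the analysis method are unaffected.
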